### Toetsing Online

The investigator will report all SAEs to the sponsor without undue delay after obtaining knowledge of the events. The sponsor will report the SAEs through the web portal *ToetsingOnline* to the accredited METC that approved the protocol, within 7 days of first knowledge for SAEs that result in death or are life threatening followed by a period of maximum of 8 days to complete the initial preliminary report. All other SAEs will be reported within a period of maximum 15 days after the sponsor has first knowledge of the serious adverse events.

### 9.3 Annual safety report

In addition to the expedited reporting of SAEs, the sponsor will submit, once a year throughout the clinical trial, a safety report to the accredited METC, competent authority, and competent authorities of the concerned Member States.

This safety report consists of:

- a list of all serious adverse events;
- a report concerning the safety of the subjects, consisting of a complete safety analysis and an evaluation of the balance between the efficacy and the harmfulness of the medicine under investigation.

#### **9.4 Follow-up of (serious) adverse events**

##### **9.4.1 (Serious) adverse event data collection**

Safety assessments will be performed and recorded by the investigators. All adverse events/reactions (solicited and unsolicited), noted by the investigators will be accurately documented in the case report form by the investigators. For each event/reaction the following details will be recorded:

1. Description of the event(s)/reaction(s)
2. Date and time of occurrence
3. Duration
4. Intensity
5. Relationship with the intervention
6. Action taken, including treatment
7. Outcome

##### **9.4.2 Assessment of causality**

The investigators are obligated to assess the relationship between study procedures and the occurrence of each AE/SAE. The investigators will use clinical judgment to determine the relationship. Alternative causes, such as natural history of COVID-19 or any underlying diseases, concomitant therapy, other risk factors and the temporal relationship of the event to the challenge will be considered and investigated. The relationship of the adverse event with the study procedures will be categorized as:

|             |                                                                                                                                                                                                               |
|-------------|---------------------------------------------------------------------------------------------------------------------------------------------------------------------------------------------------------------|
| Probable    | An adverse event that follows a reasonable temporal sequence from the challenge procedure and cannot be reasonably explained by the known characteristics of the subject's clinical state.                    |
| Possible    | An adverse event for which insufficient information exists to exclude that the event is related to the study procedure.                                                                                       |
| Not related | An event for which sufficient information exists to indicate that the aetiology is unrelated either because of the temporal sequence of events or because of the subject's clinical state or other therapies. |

#### **9.4.3 Follow-up of (serious) adverse events**

All adverse events will be followed clinically until they have been resolved, or until a stable situation has been reached. Depending on the event, follow up may require additional tests or medical procedures as indicated, and/or referral to the general physician or a medical specialist.

SAEs need to be reported till end of study within the Netherlands, as defined in the protocol as treatment discontinuation for the last patient.

### **9.5 Safety Monitoring Committee**

An independent Safety Monitoring Committee (SMC) will be appointed, including 3 individuals. Their main responsibility will be an interim analysis of all serious adverse events and occurred thromboembolisms, making the decision to halting further study procedures. A safety report including a list of all reported serious adverse events and thromboembolisms will be prepared for review by the SMC after the first 20 patients have completed follow-up and at the end of the study.

The advice(s) of the SMC will be sent to the sponsor of the study. Should the sponsor decide not to fully implement the advice of the SMC, the sponsor will send the advice to the METC that assessed the study, including a note to substantiate why (part of) the advice of the SMC will not be followed.

#### **9.5.1 Review of safety data by the safety monitor and SMC**

A safety report including information on all reported serious adverse events and thromboembolisms will be compiled after the twentieth patient has reached the fourteenth day of the study (discontinuation of treatment) and at the end of the study. These reports will be prepared in a blinded manner by a clinical investigator and sent to the SMC and all principle investigators. During a closed session, the SMC will be able to de-blind the information prior to their review.

The responsibilities of the SMC are described in the SMC Charter. In short, the SMC will evaluate the number and nature of any SAEs and thromboembolisms that occurred during the study. In the case of statistically significant increase in the number of SAEs and thromboembolisms in the intervention group, compared to the control group, the SMC will advise the sponsor to halt the study pending further review.

The advice(s) of the SMC will only be communicated to the METC when the sponsor does not follow this. With this notification a statement will be included indicating whether the advice will be followed.

### 9.5.2 Safety stopping rules

The study may be placed on safety hold for the following reasons:

- On advice of one of the principle investigators
- On advice of the SMC
- On advice of the METC that assessed the study

The safety monitor, METC, or investigators may decide to put the study on hold based on adverse events and amount of thromboembolisms, pending discussion with the safety monitor, SMC, METC and investigators. In addition, a principle investigator can always decide based on characteristics, duration and severity of signs/symptoms to treat and stop the trial for individual cases. In such cases, the principle investigator will alert the representative of the sponsor. If the METC has recommended safety hold, re-initiation of the study will require METC concurrence. The METC will be informed of a safety hold by the sponsor. Following discussion, it may be decided to terminate the study.

## **10. STATISTICAL ANALYSIS**

All patients who receive at least one study treatment (the initial dose vitamin K2 or placebo) will be included in the intention-to-treat analysis.

### **10.1 Primary study parameters**

The primary outcome of difference in dp-ucMGP (log-transformed values) will be assessed by comparing samples pre- and post-treatment using a matched-samples t-test and between groups using an independent samples t-test. Desmosine (log-transformed values) will be compared between the intervention and control groups using an independent samples t-test. Additionally, ANCOVA testing can be performed for both outcome measurements.

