#### 4.4 Sample size calculation

This is the first study evaluating the effects of oral vitamin K in COVID-19 patients. In accordance with standards for early phase clinical trials the primary outcomes of this study were chosen to facilitate a study with a relatively small sample size.

The key primary outcome will be the effect of vitamin K supplementation on elastic fiber degradation, determined by measuring plasma desmosine (pDES) in the intervention versus the control group. In the previous study of 135 COVID-19 patients pDES has a log-normal distribution, with a mean of  $\ln$  of 5.99 with a standard deviation of 0.603. The effects of vitamin K2 on this outcome have never been studied, however, we consider a difference in  $\ln(\text{pDES})$  of 10% to be clinically significant. An independent samples t-test (with  $\alpha=0.05$  and  $\beta=0.20$ ) would be statistically significant between two groups of 16 persons (total study population 32 persons).

Based on these two outcomes the sample size of 40 persons allows for a 10% loss to follow-up for the per-protocol analysis.

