### **7.5 Description and justification of route of administration and dosage**

All subjects will be treated with at least a prophylactic dosage of heparin-based (heparin or any low-molecular weight heparin) anticoagulants according to local hospital protocols.

Patients with an indication for therapeutic dosages of anticoagulants, including patients who upon admission use VKAs or DOACs, must be switched to a therapeutic dosage of heparin or any low-molecular weight heparin according to local hospital protocols and the discretion of the treating physician, prior to inclusion in the study.

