## 8. METHODS

### 8.1 Study parameters/endpoints

#### 8.1.1 Main study parameters/endpoints

- Plasma desmosine levels before and during vitamin K supplementation in intervention versus control patients
- Plasma dp-uc MGP levels before and during vitamin K supplementation within the intervention group and in intervention versus control patients

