### **10.2 Secondary and exploratory study parameters**

Adverse events will be compared by tabulating all grade 3 and 4 adverse events for each patient and calculating the proportion of in each group. The incidence of complications will be compared between groups with the chi-square test or Fishers exact test.

In the exploratory analyses, we will assess differences by comparing mean values between the groups using either a two-tailed student's t-test or non-parametric equivalents, paired if pre-treatment values are compared with post-treatment values, unpaired if comparisons are made between groups. For discrete variables (e.g. the number of positive assays), the chi-squared test or Fisher's exact test will be used (two-tailed).

As an exploratory analysis data will also be visualized on an individual patient level to evaluate the progression or correction of vitamin K deficiency in relationship to other parameters associated with COVID-19 disease severity.

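### The dp-ucMGP primary endpoint and its primary analysis include an uncontrolled before-after test within the vitamin K2 arm, which cannot show a treatment effect

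*Protocol*

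**What the plan says.** The Protocol names two primary endpoints. Desmosine is compared between arms only. The second, in section 8.1.1 and identically in the summary, is "Plasma dp-uc MGP levels before and during vitamin K supplementation within the intervention group and in intervention versus control patients".

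Section 10.1 carries this into the primary analysis: log dp-ucMGP is assessed by "comparing samples pre- and post-treatment using a matched-samples t-test and between groups using an independent samples t-test". That sentence does not name the arm for the matched test; 8.1.1 does. Log desmosine gets an independent-samples t-test between arms, and ANCOVA is allowed as an addition for both markers.

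Section 4.4 ranks the two: "The key primary outcome will be the effect of vitamin K supplementation on elastic fiber degradation". Section 10.1 does not repeat the ranking and deals with dp-ucMGP first.

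Three statements bear on how dp-ucMGP may behave without treatment:

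- Section 1.1 (assessment of vitamin K status) says that its level reflects other factors besides intake.
- Section 1.2 says that inflammation in COVID-19 could upregulate MGP and drain extrahepatic vitamin K, and names low dietary intake and use of vitamin K antagonists as evident causes of a high level.
- Section 7.5 says that patients who need therapeutic anticoagulation, "including patients who upon admission use VKAs or DOACs, must be switched to a therapeutic dosage of heparin" or a low-molecular-weight heparin before inclusion.

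**The concern.** A placebo arm is there to show what happens to the marker without vitamin K2. A matched test inside the active arm discards that information and asks only whether dp-ucMGP changed. During a hospital stay for COVID-19 it may change for reasons that have nothing to do with the study product: the disease course, food intake, or an antagonist stopped at entry.

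If such a test stands as primary evidence, a significant fall may be reported as an effect of vitamin K2 when the placebo arm fell just as much. Conversely, if dp-ucMGP rises with worsening illness, the test may hide a real benefit that the between-arm comparison would show. An analysis plan that is not at hand does not settle this, because the Protocol itself fixes both the endpoint and the test.

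**Working it through.** **1. The plan's own figure, and what its alpha covers.** Section 4.4 gives a mean ln(pDES) "of 5.99 with a standard deviation of 0.603" and takes a difference "of 10% to be clinically significant", with alpha 0.05 and 80% power.

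- Difference: 0.10 × 5.99 = 0.599
- n per arm = 2 × (1.960 + 0.842)² × (0.603 / 0.599)² = 2 × 7.85 × 1.013 = 15.9, so 16

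This reproduces the stated 16 per group with a two-sided test; a one-sided test would give 13. The 0.05 is stated here only, for desmosine. No level is given for either dp-ucMGP test, and two-tailed testing is stated only in section 10.2 for the exploratory analyses ("using either a two-tailed student's t-test or non-parametric equivalents"). The two-sided 5% used below for dp-ucMGP is therefore an assumption.

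**2. How often the paired test is significant with no drug effect.** Inputs: n = 20 in the vitamin K2 arm (section 8.2). The spontaneous drift s, in SD units of ln dp-ucMGP, and the baseline-post correlation ρ are assumptions, because the Protocol gives neither. The SD of the change is √(2(1 − ρ)), so

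- noncentrality = s / √(2(1 − ρ)) × √20, with 19 degrees of freedom and critical |t| = 2.093.

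| ρ | s | s / √(2(1 − ρ)) | noncentrality | significant |
|---|---|---|---|---|
| 0.5 | 0.3 | 0.300 | 1.34 | 24.7% |
| 0.5 | 0.5 | 0.500 | 2.24 | 56.5% |
| 0.7 | 0.3 | 0.387 | 1.73 | 37.6% |
| 0.7 | 0.5 | 0.645 | 2.89 | 78.2% |

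With s = 0 the rate is 5%. With 18 patients (20 less the 10% loss allowed in 4.4) the four rates are 22.5%, 51.6%, 34.1% and 73.3%.

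**3. Direction.** The table is symmetric in the sign of s. If dp-ucMGP drifts upward by 0.3 to 0.5 SD, the same rates apply to a significant rise, and a significant fall appears in fewer than 0.1% of null trials.

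**4. The between-arm tests.** If the drift is the same in both arms, it adds s to both means and cancels: (μ + s) − (μ + s) = 0. The between-arm test of dp-ucMGP and that of desmosine keep their nominal error rate.

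**5. Two primary markers.** If each between-arm test were run at an unadjusted 5% and either one counted as a positive trial, the family-wise error would be 1 − 0.95² = 9.75% for independent markers. Simulation gives 9.7% at correlation 0 and 7.7% at correlation 0.8.

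**The case against.** The strongest reply is that the Protocol joins the two dp-ucMGP comparisons with *and*. If both had to be significant, the randomised comparison would still guard the conclusion: in simulation (18 per arm, correlation 0.6 over time and 0.4 between markers) the false-positive rate for dp-ucMGP is 0.5% with no drift and about 3% at 0.5 SD. This is fair. The text supports that reading no less than one in which any single test suffices, but it fixes neither, and under either reading the paired test adds nothing that identifies a treatment effect.

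A reader might go further and infer several things that the document does not support:

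- *That one significant test makes the trial a success.* Under that rule, the chance of at least one false positive among the two between-arm tests and the paired test is about 13% with no drift, 34% at 0.3 SD and 64% at 0.5 SD. The Protocol states no such rule, so these are not its error rates.
- *That a fall in dp-ucMGP is to be expected.* Section 1.2 says only that inflammation could have this effect. Section 1.1 says that insufficiency may develop within days of poor intake, section 6.4 notes poor appetite and hospital nutrition low in vitamin K, and section 9.2.2 says that symptoms often progress after admission. In the earlier cohort (Figure 2), 60 of 135 patients, or 44%, had a poor outcome. A rise is equally possible.
- *That the absence of an alpha rule is an error.* A testing order is commonly left to the analysis plan, which is not shown.
- *That natural recovery undermines the desmosine result.* That test is between arms only.

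**Conclusion.** The point holds for the within-arm comparison. The dp-ucMGP primary endpoint and analysis contain an uncontrolled test that cannot attribute a change to vitamin K2, and the Protocol supplies the reasons why the marker may move without it. The 25% to 78% range rests on assumed drifts of 0.3 to 0.5 SD, assumed correlations of 0.5 to 0.7, n = 20 and a two-sided 5% level. It shows how easily the paired test can mislead and is not an estimate for this trial.

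The damage is confined to what may be claimed about dp-ucMGP. The randomised comparisons stand.

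A secondary point is one of consistency: section 4.4 gives desmosine priority, and section 10.1 does not carry this through. The 9% to 10% family-wise error of two unadjusted between-arm tests applies only if either may count as a win, so it is a reason to state which result the main conclusion rests on, not a demonstrated excess of error.

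**What to change.** 1. In the summary and section 8.1.1, strike the clause on the intervention arm alone from the dp-ucMGP primary endpoint, leaving intervention versus control.
2. In section 10.1, remove the matched-samples t-test as primary evidence. Base the primary dp-ucMGP comparison on the between-arm contrast, preferably the ANCOVA that 10.1 already allows, with log baseline dp-ucMGP as covariate (10.1 names no covariate), and state the two-sided level.
3. Report before-after changes descriptively, with confidence intervals, for both arms side by side.
4. Add one sentence to 10.1 saying that the trial's main conclusion rests on the between-arm desmosine test, in line with 4.4. Whether dp-ucMGP is then tested formally, and under what alpha or order, is for the sponsor or the analysis plan. Testing it only after a significant desmosine result would hold family-wise error at 5% with 16 per arm unchanged, but would make a claim on the direct marker of vitamin K status depend on an outcome for which the effect of vitamin K2 has not been studied.

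Cost: wording only, before unblinding. No added patients, samples or visits, and the desmosine power is untouched. What is lost is the option to present a significant within-arm change as a primary result.

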### **8.3.6 Dp-ucMGP**

At baseline (within 24 hours of inclusion) and subsequently three times per week, EDTA plasma will be frozen at -80 degrees Celsius for retrospective determination of dp-ucMGP. Circulating dp-ucMGP levels will be determined using the commercially available IVD CE marked chemiluminescent InaKif MGP assay on the IDS-iSYS system (IDS, Boldon, UK). 50 µL of patient sample or calibrators are incubated with magnetic particles coated with murine monoclonal dpMGP antibody, an acridinium labelled murine monoclonal ucMGP antibody and assay buffer. The magnetic particles are captured using a magnet and a wash step performed to remove any unbound analyte. Trigger reagents are added, the resulting light emitted by the acridinium label is directly proportional to the concentration of dp-ucMGP in the sample. The within-run and total precision of this assay is 0.8 – 6.2% and 3.0 – 8.2%, respectively. The assay measuring range is between 300 – 12,000 pmol/L and was previously found to be linear up to 11,651 pmol/L. Dp-ucMGP values below 500 pmol/L are considered to be in the normal healthy range.

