### **8.3.8 Desmosine**

The rate of elastin degradation will be quantified by measuring plasma (p)DES levels. At baseline (within 24 hours of inclusion) and subsequently three times per week, EDTA plasma

will be frozen at -80 degrees Celsius for retrospective determination of pDES. Subjects with the highest pDES are assumed to have the highest rates of elastin degradation. Isodesmosine and desmosine fractions will be measured separately by liquid chromatography-tandem mass spectrometry as previously described using deuterium-labelled desmosine as internal standard [57, 58].

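### Section 10.1 makes an unadjusted t-test the between-arm test for both primary outcomes and leaves baseline-adjusted ANCOVA optional; the t-test is valid, but ANCOVA would be more precise at almost no cost

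*Protocol*

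**What the plan says.** For the outcome that section 4.4 puts first ("The key primary outcome will be the effect of vitamin K supplementation on elastic fiber degradation"), section 10.1 states: "Desmosine (log-transformed values) will be compared between the intervention and control groups using an independent samples t-test". For dp-ucMGP it plans "comparing samples pre- and post-treatment using a matched-samples t-test and between groups using an independent samples t-test". It then adds, for both outcomes: "Additionally, ANCOVA testing can be performed for both outcome measurements". It gives no covariate, no condition for running ANCOVA and no statement of its role. It does not say whether the between-arm t-test uses the on-treatment level or the change from baseline, or at which time point.

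The baseline value is scheduled for everyone. Section 8.3.8 on desmosine reads "At baseline (within 24 hours of inclusion) and subsequently three times per week, EDTA plasma", and section 8.3.6 sets the same schedule for dp-ucMGP. The desmosine endpoint in section 8.1.1 is "Plasma desmosine levels before and during vitamin K supplementation in intervention versus control patients".

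Section 4.4 sizes the trial on an independent samples t-test of ln(desmosine). It uses mean 5.99 and SD 0.603 from an earlier cohort ("In the previous study of 135 COVID-19 patients pDES has a log-normal distribution") and arrives at 16 per arm. Enrolment is 40, with an allowance for 10% loss.

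**The concern.** The baseline value of a biomarker is usually the most informative covariate available. Here the protocol collects it, names it in the endpoint, and then sets a between-arm test with no term for it. The analysis that would use it is left to discretion. In a 40-patient trial the lost precision can matter.

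The loose status of ANCOVA is a second, smaller matter. A reader of the final report could not tell from the protocol how much weight an ANCOVA result was meant to carry if it disagreed with the t-test.

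**Working it through.** **Inputs.** Mean ln(desmosine) 5.99, SD 0.603, 10% difference, alpha 0.05 and beta 0.20 (section 4.4). Planned difference: 0.10 × 5.99 = 0.599. Evaluable patients after 10% loss: 40 × 0.9 = 36, or 18 per arm. Assumptions: two-sided test (sidedness is not stated for the primary test), the same SD at baseline and follow-up, and a baseline-to-follow-up correlation ρ, which the protocol does not give and which is shown from 0 upwards.

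**Step 1: the plan's own figure.** n per arm = 2 × (0.603 × (1.960 + 0.842) / 0.599)² = 15.9, rounded up to 16. This reproduces the protocol. It rests on the SD of a level, so it fits an unadjusted comparison of levels. With the noncentral t distribution, power is 77.6% at 16 per arm, 82.5% at 18 and 86.5% at 20.

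**Step 2: variance under the three possible analyses.** With σ = 0.603:
- t-test on levels: σ²
- t-test on changes: 2σ²(1 − ρ)
- ANCOVA on baseline: σ²(1 − ρ²)

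Relative to ANCOVA, levels cost a factor 1/(1 − ρ²) and changes a factor 2/(1 + ρ). Neither factor is below 1.

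**Step 3: power at 18 per arm for 0.599** (noncentral t; df 34 for the t-tests, 33 for ANCOVA).

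| ρ (assumed) | ANCOVA residual SD | t-test, levels | t-test, changes | ANCOVA |
|---|---|---|---|---|
| 0 | 0.603 | 82.5% | 54% | 82% |
| 0.3 | 0.575 | 82.5% | 69% | 86% |
| 0.5 | 0.522 | 82.5% | 82.5% | 92% |
| 0.7 | 0.431 | 82.5% | 96% | 98% |

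Simulation, which also allows for chance imbalance in the covariate, puts ANCOVA up to about one point lower (81%, 85%, 91%, 98%). At ρ near 0 adjustment therefore gains nothing and costs about one point. By the normal approximation of step 1, n per arm for 80% power falls from 16 to 15, 12 and 9 at ρ = 0.3, 0.5 and 0.7.

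**Step 4: worst case for the open choice.** Null trials were simulated at 18 per arm, counting success if either the t-test on levels or ANCOVA gave p < 0.05. Type I error was 5.6%, 6.3%, 7.3% and 8.3% at ρ = 0, 0.3, 0.5 and 0.7. Allowing for simulation error, the range is about 5.5% to 8.4%. Each test used alone held about 5%.

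**Step 5: chance baseline imbalance.** With 20 per arm, the standard error of the baseline difference is 0.603 × √(2/20) = 0.19. Only ρ times an imbalance is expected to carry into follow-up: 0.3 × 0.19 = 0.06 to 0.7 × 0.19 = 0.13, which is 10% to 22% of 0.599.

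**The case against.** The best case for the protocol is that it already has a valid primary test. Section 10.1 commits to the t-test and only permits ANCOVA as an addition, and section 4.4 sizes the trial on that t-test. On the protocol's own inputs the test has more than 80% power at 18 per arm. All of this stands, and it rules out several stronger readings.

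- A reader might infer that the plan has two competing primary p-values and so a type I error of 7% or 8%. The difference between a firm commitment and a permission, together with the sizing, makes the t-test the planned test, at 5%. The inflation in step 4 arises only if that order is ignored.
- A reader might infer that baseline is discarded altogether. For dp-ucMGP it enters the paired pre/post test, although that is a within-arm comparison. For the between-arm tests the text does not exclude change scores, although the SD of 0.603 points to levels for desmosine.
- A reader might infer that baseline imbalance biases the result. In a randomised trial the unadjusted t-test is unbiased, and its standard error already covers chance imbalance. The 0.19 in step 5 should not be set directly against the planned effect.
- A reader might infer a large gain. That depends on a correlation the protocol does not give. In acutely ill inpatients with an expected average stay of 6 days (section 3), a low value cannot be excluded.

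Naming covariates and model form may also be left to an analysis plan that is not at hand. What remains is that the protocol itself assigns the primary between-arm role to the less efficient test.

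**Conclusion.** The point holds as one of efficiency and clear pre-specification. It does not show an invalid analysis or a wrong sample size. At 18 per arm and a difference of 0.599, baseline-adjusted ANCOVA is expected to change power from 82.5% to between about 82% (no correlation) and 98% (correlation 0.7). If the t-test was meant for changes, ANCOVA is again at least as good, and clearly better at low to moderate correlation.

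The power figures apply to desmosine only, because the protocol gives no SD for dp-ucMGP; the variance ratios in step 2 apply to both outcomes. All figures rest on an assumed correlation, equal SDs at the two times and a two-sided test. The change should be made, but the trial does not depend on it.

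**What to change.** In section 10.1, replace the sentence that permits ANCOVA with: *The primary between-arm analysis of each outcome is ANCOVA of the ln on-treatment value at one pre-specified time point, adjusted for the ln baseline value, reported as a ratio of geometric means with 95% CI; the unadjusted t-test is a sensitivity analysis.* Reword the existing t-test sentences to match.

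The time point must be named. Samples are taken three times a week, and without a fixed time ANCOVA is no better specified than the t-test. Name this one model only: offering a longitudinal model as an alternative would reopen the choice. No further covariate is needed.

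The cost is one degree of freedom per analysis and no extra samples, visits or patients. The sample size in section 4.4 can stay, since sizing on the unadjusted test is conservative for ANCOVA unless the correlation is close to zero, where the loss is about one point of power. The change should be in place before unblinding.
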